## Discussion

Currently there are two published studies, which prospectively evaluate rehabilitation following RTSA. Hagen et al. have reported results from a randomised controlled blinded study regarding following RTSA assessing early versus delayed mobilization, and conclude that early mobilization is safe, and may offer advantages to the elderly population [31]. Lee et al. reported that not using a sling following RTSA resulted in non-inferior outcomes as compared to sling immobilization for 3 or 6 weeks [32]. Whilst these studies illuminate the potential benefit of an early and accelerated rehabilitation strategy, they do not address the question of how the rehabilitation should be structured, specifically whether formal physical therapy is required or if the rehabilitation can be conducted effectively through a surgeon directed home exercise program. An ideal rehabilitation strategy following RTSA optimizes outcomes while minimizing cost and inconvenience to patients. Thus, the necessity for formal, clinic-based physical therapy should be determined. This study proposes to answer this question with a large prospective, multi-center, randomised controlled trial across several regions of the United States producing generalizable results. If the HT group has the same or better outcomes than the formal PT group, then surgeon-directed home therapy is a convenient and cost-effective rehabilitation strategy for patients who have undergone RTSA. If the PT group has better outcomes without increased harm/complications to patients, then a studied rehabilitation strategy can be endorsed. The prospective and randomised nature of the project are strengths, whilst the cross-over option allows for patient preference and safety.

One limitation of the project is that all participating surgeons are fellowship trained shoulder surgeons and therefore have special training in performing RTSA. Therefore, results of the surgery and instruction in a home therapy program may not be generalizable to all orthopedic surgeons. A second limitation is that there may be variability of outcomes introduced by therapists in out-patient clinics drifting from the provided rehabilitation guidelines. An attempt at fidelity to the physical therapy intervention is attempted by providing rehabilitation guidelines and therapist training instruction booklets to all treating therapists; however, PT interventions for each patient are not being individually monitored to discern how closely therapists follow the rehabilitation guidelines. However, this somewhat pragmatic approach to out-patient physical therapy renders the results for this group generalizable. A limitation of the HT group is that the method of delivery of instruction of the exercises by surgeons and clinical research assistants at post-operative visits may vary across sites which could introduce variance.

In summary, this project will compare clinical and patient reported outcomes, costs and complications for PT versus HT over a two-year period following RTSA to aide in determining the optimal safe and value-based rehabilitation strategy.

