We aim to compare outcomes for formal, clinic-based physical therapy (PT group) to home therapy, in which patients are provided with instructions from surgeons at post-operative appointments (HT group) by using a superiority, randomised design [34]. Findings will aid in determining the potential role of formal PT in the RTSA recovery process, and secondarily, will evaluate a formal RTSA rehabilitation protocol, which is standardized for the trial [20].. Findings from the study may assist in evaluating the financial benefit or burden of formal PT in the RTSA recovery process and determine the resource necessity of PTs in a traditional clinical environment. We hypothesize that the PT group will demonstrate superior clinical and patient reported outcomes, significantly quicker levels of recovery, and significantly higher levels of overall recovery at our long-term outcomes capture when compared to the HT group. Secondary aims of this project include analysis of the incidence of complications between the two groups, specifically acromial stress fractures and prosthetic instability events, which we hypothesize will be higher in the PT group; and cost of care which we hypothesize will be higher in the PT group.

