#### Primary outcomes

The American Shoulder and Elbow Surgeons (ASES) questionnaire is a standardized method of evaluating shoulder pain and function. This instrument is a 100-point scale which assesses pain (50 points) and activities of daily living (50 points), and has demonstrated good reliability/validity following shoulder arthroplasty [38]. The ASES score clinically important change following shoulder arthroplasty is 9 to 10 points [11, 39].

Pain level is monitored using the 0–11 numeric pain rating scale (0 = no pain; 10 = worst pain imaginable) at present, as well as the best and worst rating over the 2 week interval preceding assessment.

The Single Assessment Numeric Evaluation (SANE) score asks a patient the question: “How would you rate your affected joint/region of interest today as a percentage of normal (0% to 100% scale) with 100% being normal?” and has been validated for patients having shoulder arthroplasty [40].

The Patient-Reported Outcomes Measurement Information System (PROMIS-29) version 2 .0 profile assesses pain intensity (0 to 10) as well as seven health domains including physical function, fatigue, pain interference, depressive symptoms, anxiety, social interactions, and sleep disturbance with 4 items per domain. The physical health factor (physical function, pain intensity and interference, and social interactions) and mental health factor (anxiety and depressive symptoms) have been established as valid and reliable [41]. The PROMIS has been determined to be a responsive instrument following RTSA [42].

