### Statistical analysis

#### Sample size

To determine sample size of this parallel design, the study was powered (a-priori) for the primary outcome measure of the American Shoulder and Elbow Surgeon (ASES) scale at baseline, 2 and 6-weeks, 3 and 6 months post replacement. Study assumptions estimate a 12 month ASES score of 79/100 for the PT group (SD = 15.0) and 69/100 for the HT group (SD = 15.0). The 10 point change is considered a clinically meaningful difference in groups [10].

Assuming normal distributions among the 2 independent group ASES measures, and assuming small-to-medium effect based on between-group differences, we constructed a sample size estimation using a Repeated Measures Analysis of Covariance (ANCOVA). Measuring fixed effects, main effects, and interactions, with an expected 80% power, 6 dedicated time intervals (including baseline), two independent groups, 2 covariates, 1 outcome measure, and a standard error of probability of 0.05, we estimate the need for a minimum sample size of 158 for statistical significance (~ 79 per group). To account for the expected potential 24 crossover (15%) subjects, we will increase enrollment to 182 total. Missing values will be adjusted using a chains equation, multiple imputation method in which we will assign predictor, structural and impute variables.

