#### Data analysis primary outcomes

Study data are collected by clinical research assistants and managed using REDCap electronic data capture tools at the lead institution site (Rush University Medical Center). REDCap (Research Electronic Data Capture) is a secure, web-based software platform designed to support data capture for research studies, providing 1) an intuitive interface for validated data capture; 2) audit trails for tracking data manipulation and export procedures; 3) automated export procedures for seamless data downloads to common statistical packages; and 4) procedures for data integration and interoperability with external sources [36].

Chi square and t-tests will be used to measure differences in baseline characteristics of both groups. Linear mixed effects modeling will be used to measure differences in the outcomes associated with ASES scores, pain, SANE, and range of motion measures across all time points. Linear mixed effects modeling is robust to individual changes, allows for control of variables that are different at baseline, and allows for control of variables that influence outcomes. Linear mixed effects modeling is not bound by the same assumptions as OLS modeling methods (e.g., ANOVA). Differences will be captured for up to 6 time points (pre op to post at 2 and 6 weeks, 3, 6, 12 and 24 months). A *p* value of < 0.05 will be considered statistically significant for all analyses.

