We will evaluate the primary outcomes with two sets of statistical analyses: One with intention to treat including patients who crossed over and a second adjusted to the cross-overs of the patients. Non-adherence to randomly assigned treatments can often mean that the intention-to-treat analysis underestimates the real benefit of the treatment [48]. We will run a preplanned sensitivity analysis evaluating the descriptive statistics of those who crossed over to those who did not. We will also run an estimated “as treated” longitudinal analysis based on comparisons of those actually treated with PT and HT. We will analyze a repeated measures, linear mixed effect model in which our outcomes will remain the dependent variable and treatment received will be incorporated as a time varying covariate. Adjustments will be made for the time of cross-over with respect to the original enrollment date to approximate the designated follow-up times. Baseline variables that were individually found to predict missing data or treatment received will be included to adjust for possible confounding.

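### The Discussion draws a positive conclusion for home therapy from 'the same' outcomes, but this superiority trial has no margin or interval rule that defines 'the same'

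*Protocol article*

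**What the plan says.** The Background sets the framework: outcomes are compared "by using a superiority, randomised design", and "We hypothesize that the PT group will demonstrate superior clinical and patient reported outcomes". The Sample size section assumes 12-month ASES means of 79 (PT) and 69 (HT) with SD 15, treats the 10-point gap as clinically meaningful, and arrives at 158 patients, raised to 182 for crossover. Under Data analysis primary outcomes, a p "value of < 0.05 will be considered statistically significant for all analyses". The complications and cost sections use the same threshold for difference tests.

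The Discussion then looks ahead to the result. The condition it sets is "If the HT group has the same or better outcomes than the formal PT group". The conclusion it attaches to that condition reads "then surgeon-directed home therapy is a convenient and cost-effective rehabilitation strategy". Nothing in the article defines the same outcomes. The nearest benchmark is under Primary outcomes: "The ASES score clinically important change following shoulder arthroplasty is 9 to 10 points".

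The Eligibility section allows crossover when there is concern about safety, compliance or outcome. It plans for about 15% and cites earlier research that planned 10% and reached 30%. The analysis section acknowledges the consequence: "Non-adherence to randomly assigned treatments can often mean that the intention-to-treat analysis underestimates the real benefit of the treatment". It adds a crossover-adjusted analysis and an as-treated mixed model.

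**The concern.** A superiority test can show that PT is better. Failing to show it does not establish that HT is as good. The article states what will be concluded if outcomes are the same, but supplies only difference tests at p < 0.05. 'Better' could come from a significant result in favour of HT. 'The same' could come only from a non-significant one.

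The Discussion says the trial should settle whether formal PT is required, so this is the conclusion most likely to affect practice. Crossover pulls the ITT difference towards zero, in the direction that favours it. This is a mismatch between the framework and the conclusion, both fixed in this document, so it is not a detail that an article would leave to an analysis plan.

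**Working it through.** **Inputs.** From the Sample size section: SD 15, difference 10, 79 per arm before inflation and 182/2 = 91 per arm after it. From Eligibility: crossover share c = 0.15 planned, 0.30 in the precedent. From Primary outcomes: important change 9 to 10 points. My assumptions: two-sided 5% level, a two-sample t comparison at 12 months, no covariate gain, and a true PT advantage of 7 as an intermediate case.

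**The plan's own figure.** 158 + 24 = 182 reproduces. The 158 follows from an ANCOVA calculation with effect size f = 0.25 and 2 numerator degrees of freedom (power 0.802), neither of which is stated. The stated 10 points with SD 15 would need only 36 per arm. Nothing below depends on how 158 was reached.

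**Step 1: what a non-significant result leaves open.** Half-width = t(0.975, 2n − 2) × 15 × √(2/n). The highest upper limit that a non-significant result can have is twice that.

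| Evaluable per arm | Half-width | Highest upper limit |
|---|---|---|
| 91 | 4.39 | 8.8 |
| 86 | 4.52 | 9.03 |
| 79 | 4.71 | 9.4 |
| 69 | 5.05 | 10.1 |

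With complete data at 91 per arm, a non-significant interval stays just under 9. It passes 9 at 86 or fewer, a loss of 5 per arm (5/91 = 5.5%). The sample size is inflated for crossover only, with no allowance for attrition.

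**Step 2: how crossover changes the chance of a non-significant result.** Full dilution assumes that every crossover, in both arms, gets the whole effect of the other treatment: ITT difference = δ(1 − 2c). Mild dilution is taken as δ(1 − c). The probabilities come from the noncentral t distribution at 91 per arm.

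| True PT advantage | No crossover | c = 0.15, mild to full | c = 0.30, mild to full |
|---|---|---|---|
| 7 | 12% | 24% (ITT 5.95) to 41% (ITT 4.9) | 41% (ITT 4.9) to 76% (ITT 2.8) |
| 10 | 0.6% | 3% (ITT 8.5) to 12% (ITT 7) | 12% (ITT 7) to 57% (ITT 4) |

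**Step 3: which margin would do any work.** The rule is that the upper 95% limit for PT minus HT lies below margin M.

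- At 91 per arm with M = 9, an observed PT advantage up to 9 − 4.39 = 4.61 passes. Significance starts at 4.39. Every non-significant ITT result would pass, and an observed 4.5 would be both significantly in favour of PT and 'the same'.
- With M = 7, the pass limit is 7 − 4.39 = 2.61, so results between 2.61 and 4.39 are inconclusive.
- The smallest margin with 80% power when the true difference is zero is (1.96 + 0.8416) × 15 × √(2/91) = 6.2 points, before dilution.

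**Step 4: why ITT alone is not enough.** If PT is truly 10 points better and crossover is 30% with full dilution, the ITT difference is 4. The chance of passing is Φ((M − 4)/2.224 − 1.96), which is 61% at M = 9 and 27% at M = 7.

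**The case against.** The sentence is a forward-looking remark in a Discussion, and the analysis sections contain no rule equating non-significance with sameness. A reader might infer that the trial has a decision rule to endorse home therapy. The text does not support that: endorsement is the article's word for the PT-better outcome only, and dropping formal PT is nowhere stated. That a null result would be read as sameness is an inference, though the article offers no other criterion.

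A reader might also infer that poor adherence alone would produce the conclusion. The plan has a crossover-adjusted analysis and an as-treated model with adjustment for predictors of treatment received, so ITT is not the sole basis. That stands. But these are not randomised comparisons, crossover may be prompted by outcome, and they set no criterion for sameness.

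A third tempting reading is that a null result at planned enrolment would leave a 9-point PT advantage open. With all 91 per arm evaluable it would not (8.8), nor at 100 per arm, the abstract's 200 patients (8.4). It needs 86 or fewer per arm, or a larger SD.

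Finally, the upper ends of the crossover ranges are worst cases, and the planned mixed model uses all visits. Both points are fair, which is why ranges are shown.

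**Conclusion.** The point holds at moderate severity. The article names superiority as its only framework and p < 0.05 as its only criterion, yet attaches a positive conclusion to an undefined 'same'. A null result could stand as sameness without any test of it.

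How much this matters depends on crossover and attrition. With little of either and a true PT advantage of 10, a misleading null is rare (0.6%). With a true 7, or crossover nearer the cited precedent, it becomes common. These figures rest on SD 15, 91 per arm, a single-time-point comparison and the assumed dilution. Randomisation, conduct and the primary superiority test are unaffected; what needs changing is what may be concluded.

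**What to change.** Reword the Discussion so that a non-significant result is reported as superiority of PT not shown, with the 95% confidence interval for PT minus HT on 12-month ASES. This alone removes the error.

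If the team wants to be able to say 'same' or 'not worse', add one paragraph that:

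- fixes and justifies a margin now, below the 9 to 10 point important change. Exactly 9 would be idle on ITT at 91 per arm; about 6 to 7 is within reach of 182 patients before dilution (6.2 at 80% power);
- requires the upper 95% limit to lie below it in both ITT and one named crossover-corrected analysis;
- labels any other non-significant result inconclusive.

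The precision of the corrected analysis should be checked when it is chosen. For example, an estimator that rescales ITT by 1/(1 − 2c) has a smallest 80%-power margin of 6.23/0.70 = 8.9 at 15% crossover and 6.23/0.40 = 15.6 at 30%, so high crossover would rule out a claim of sameness.

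The cost is one paragraph and no extra patients for the rewording or for a margin of that size on ITT. The downside is that some null results must be called inconclusive.

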## Data Availability

Not applicable.

## Abbreviations

RTSA: Reverse total shoulder arthroplasty
PT group: Physical therapy group
HT group: Home therapy group
ASES: American Shoulder and Elbow Surgeons
SANE: Single alpha-numeric evaluation
OA: Osteoarthritis
ATSA: Anatomic total shoulder arthroplasty
SPIRIT: Standard Protocol Items Recommendations for Interventional Trials
REDCap: Research Electronic Data Capture
PROMIS: Patient-Reported Outcomes Measurement Information System
ER0: External rotation at 0 degrees of abduction (arm at the side)
ER90: External rotation at 90 degrees of abduction
IR: Internal rotation
ICC: Inter-tester correlation coefficient
ICM: International Consensus Meeting
ANCOVA: Analysis of covariance
QALY: Quality-adjusted life years
